#### Qualitative analysis

All qualitative data will be analysed using Framework Analysis [61]. Initial themes and concepts will be identified through reviewing the data. These will then be used to construct a thematic index, used to assign a label to each phrase or passage. The labelled raw data will then be summarised and synthesised into the thematic charts. This matrix-based method of analysis will facilitate systematic exploration of the range of views including both between cases and within cases in order to produce both descriptive and explanatory accounts of the data. To minimise potential bias, a second analyst will independently index a proportion of transcripts and analyse the matrix-based material.

#### Economic evaluation analysis

This pilot economic evaluation study has the objective of detecting problems in the cost collection, exploring how patients respond to the primary outcome in the study, the GHQ-12, and comparing it to the EQ-5D-5 L instrument, as well as developing the economic evaluation model that will be applied to a phase III RCT. The pilot economic evaluation will compare incremental costs to incremental health gains of the PEER arm versus USUAL arm. Due to the very low numbers, this will be strictly an exercise to detect problems in the process of data collection and development of the full economic evaluation model. The rationale is to use the feasibility stage data to prepare a future full trial cost-effectiveness.

For the costs, we will use data collected on the CSRI on service use (including health, social, and voluntary services) and associated costs at 4 and 10 months post-randomisation. Unit costs of resources used will be derived from routine sources locally where possible and from national sources such as the NHS reference costs.

Health gains will be obtained from the answers to both the GHQ-12 and to the EQ-5D-5 L instruments. The gold standard for economic evaluation is to use generic health state outcome measurements because these allow comparability across clinical areas. Thus, we will run two types of pilot economic evaluation analyses. First, we will run a pilot cost-effectiveness analysis based on the GHQ-12. Second, we will perform a pilot cost-utility analysis using quality-adjusted life years (QALYs) gained based on the answers to the EQ-5D-5 L. Additionally, since there is limited evidence on how the GHQ-12 and EQ-5D-5 L relate to each other [38], we will use the pilot data to explore the correlation of these two instruments in terms of health gains in different domains.

With the pilot cost and outcome data, we will explore the calculation of confidence intervals for costs and health gains using non-parametric bootstrapping, with the understanding that low numbers preclude generalisability. Also, we will explore the application of probabilistic sensitivity analysis that will eventually generate cost-effectiveness acceptability curves in a Phase III RCT. These curves graphically represent provisional estimates of the cost-effectiveness of the intervention.

#### Fidelity

Videotaped sessions will be rated against fidelity checklists. Fidelity of the peer befriending training and supervision to the training manual and the peer befriending intervention to the peer befriending handbook will be evaluated by calculating a per cent fidelity score (components implemented/components planned × 100). Inter-rater (two raters) and intra-rater reliability will be calculated for all three session types. Inter-rater agreement coefficients will be used to calculate inter and intra-rater reliability. Counts of sessions completed will indicate whether befriender/befriendee pairs have adhered to the six befriending visits.

### Data management

The main trial database will be hosted at King’s Clinical Trials Unit (KCTU). Data will be managed using the InferMed MACRO database system. This system is regulatory compliant (GCP, 21CRF11, EC Clinical Trial Directive). Data will be entered by authorised staff (Trial Manager and research assistants) with a full audit trail in which participants will be identified by their unique PIN. The database will include feasibility data on people consented, with these data being aggregated where we do not have consent to hold participants’ data (for example, reasons for declining participation), as well as assessment and outcome measures data, and serious adverse event data.

A separate database storing intervention details will also be hosted at KCTU. This will include all necessary information on the intervention each participant in the PEER arm received as extracted by visit record forms and information from supervision sessions (e.g. number of sessions arranged, completed, missed and reason why; duration of session; topics discussed). The intervention database will meet the same requirements as the main trial database above, but only the Trial Manager will be authorised to input data and have access. Trial statisticians will only have access after unblinding. Data in the second database will be extracted and summarised routinely by an unblinded statistician independent to the trial when necessary.

Fidelity data, qualitative data, and health economic data will be kept at City, University of London, on a secure network drive within the City system, which is regularly backed up. The fidelity dataset will be anonymised with participants being identified by their PIN. The Trial Manager and unblinded researchers analysing fidelity data will have access to it. Qualitative data will be transcribed and then saved by the qualitative research assistant in an electronic database. Participants in the qualitative data database will be identified by their unique PIN; however, this database will also include identifying information, such as gender and age. Health economic data will be entered onto a password-protected Excel spreadsheet. Each participant on this spreadsheet will be identified by their PIN. Qualitative and health economics data will be accessible by the Trial Manager and qualitative and health economics researchers.

### Site monitoring

The Trial Manager will conduct on-site/central monitoring. The Trial Manager will do monthly checks on data completeness and range checks as outlined in the data management plan. In addition, regular checks of a selected number of participant records will be done at three monthly intervals to check that data recording procedures are being followed consistently and accurately. The data will also be perused by the trial statistician when extracted for Data Management Committee reports and at the end of the study. Data queries will be raised by the trial statistician and sent to the Trial Manager for resolution. Any issues found in any of these checks will be resolved against the original source records and corrected in the MACRO database where possible.

### Anticipated risks and benefits

The risk of harm is considered unlikely to participants and low risk, which was further confirmed by early user consultation. Research assistants and peer befrienders visiting participants with aphasia will have a Disclosure and Barring Service (DBS) check, to ensure participant safety. There are no formal statistical criteria for stopping the trial early. Decisions to stop the trial early on grounds of safety or futility (with regard to recruitment) will be made by the Trial Steering Committee on the basis of advice from the Data Management Committee.

Some participants may experience fatigue and poor concentration during assessment sessions. To minimise this, information will be provided in an accessible aphasia-friendly way and researchers will offer breaks as and when needed. It will also be made clear to participants that they can request a break at any time or additional visits to complete outcomes.

There is the risk that participants may become burdened with their involvement in the study. Participants may get upset during assessment and/or outcome measurement, or peer befriending visits. All researchers and peer befrienders will be trained and supervised to deal with these situations, for example they may take a break, see if the participant wants to talk about their feelings, or stop the session if needed. Issues raised by peer befrienders will be discussed in monthly supervision with the befriender facilitator, with additional individual support provided as needed. If a participant or peer befriender scores within the high emotional distress range of the GHQ-12 (3 or more) or the GHQ-28 for significant others (6 or more), the research assistant or Trial Manager will discuss with them their score and ask them to consider talking to their GP. If they would like, they will be given information on local support organisations and groups. For peer befrienders who score within the high emotional distress range of the GHQ-12, the Trial Manager will explore with them whether they find peer befriending distressing and whether they need to be withdrawn from the study.

In terms of benefits, participants in this study will receive all their usual care; no treatment will be withdrawn due to participation in the study. Information about local support services and voluntary organisations that support well-being post-stroke will be offered to those experiencing low mood and it will also be offered if participants express feelings of loneliness and social isolation. Trained befrienders will also be linked to local support organisations, where their skills can be used in the future to support people with aphasia.

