#### Participants with aphasia

Inclusion criteria for participants with aphasia are as follows:Over 18 years of age.Fluent premorbid users of English (confirmed by relative or self-report).Presence of aphasia due to stroke: determined by the multidisciplinary team notes, based on SLT diagnosis. In cases of uncertainty, i.e. where there is no SLT diagnosis at the time of recruiting to the trial, CRN nurses will use the Frenchay Aphasia Screening Test [29] for screening for aphasia. In these cases, the presence of aphasia will be determined based on the published cut-offs in the Frenchay Aphasia Screening Test manual.Low levels of emotional distress. This aims to ensure that participants do not require more complex psychological interventions. To determine the level of emotional distress, the Depression Intensity Scale Circles (DISCS) [30] will be used. This tool is recommended for people with communication problems, cognitive deficits, and visual perception problems post-stroke [31]. Scores on DISCS range 0–5, with a score of 0–1 indicating no/low distress and a score of ≥ 2 used as a cut-off for identifying depression in those with complex disabilities following brain injury [30]. Those scoring 0–1 will be eligible for the study. If a participant scores ≥ 2 on DISCS, they will be referred back to the multidisciplinary team for consideration for more complex psychological care as appropriate. People who score 2 (which is also the median on DISCS) and who the multidisciplinary team deems do not need other psychological care or other psychological care is not available will still be eligible to take part. If a person scores 3 if screened while still in the hospital, and is uncertain about their level of emotional distress or feels they will be better once home, consent will be obtained to re-screen them for eligibility when they return to the community (second screen). If at the second screen they score 0–1, or 2 as described above, then they will be eligible to take part.

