#### Patient-reported outcome measures

A range of outcome measures will be used with participants with aphasia covering mood, wellbeing, activities, and communication and social participation. Measures chosen have either been developed specifically for neurologically impaired populations, some including people with aphasia or have been previously used with people with aphasia with good evidence of accessibility and acceptability. Where appropriate, the presentation of measures will be modified to make them aphasia-friendly in line with best practice guidelines [48]. The content, however, will not be changed to avoid affecting measures’ psychometric properties.

The following primary outcomes for participants with aphasia will be completed at baseline, 4 and 10 months post-randomisation: General Health Questionnaire-12 (GHQ-12) [32], using 0 0 1 1 scoring and the Depression Intensity Scale Circles (DISCS) [30]. The DISCS is being measured because some participants may not be able to complete the GHQ-12. This feasibility study will assess how often this is the case. The DISCS will be treated as the primary outcome measure only if there is ≥ 10% missing data in the GHQ-12 due to severity of aphasia; otherwise, DISCS will be a secondary outcome measure.

The following secondary outcomes for participants with aphasia will be taken at the same time points: Short Warwick Edinburgh Mental Well-being Scale-7 [49], Communicative Participation Item Bank [50], Community Integration Questionnaire—Adapted [51]. Proportion with high emotional distress vs low emotional distress as measured using the GHQ-12 (high distress = score of 3 or more, low distress = score of 0–2). There are additional psychological constructs that may be affected by peer befriending; however, the evidence base is not strong on whether existing measures on these constructs are responsive to change when used with people with aphasia. We will include two exploratory self-report outcomes for participants with aphasia in this study, the Communication Confidence Rating Scale for people with aphasia [52, 53] and the Friendship Scale [54] in order to see whether they may be suitable to use as secondary outcome measures in a definitive trial. These will be completed by participants with aphasia at each of the three time points.

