### Sample size

We will recruit in total 60 participants with aphasia (30 in each arm of the study). Allowing for a ~ 15% lost to follow-up rate, at least 50 will complete the study. With 60 participants recruited, we will be able to estimate a 95% confidence interval for the recruitment rate to within approximately 25%. This sample size will be adequate to estimate important parameters needed to inform the design and the sample size of a full trial, such as the standard deviation, consent rates, event rates. This sample size also meets recommended sample sizes for feasibility studies [59].

Although this is a feasibility study, we would like to estimate exploratory differences between the PEER and USUAL arms. If we assume we retain 50 participants at follow-up, a two-sided test, *α* = 0.05, and independence of participants, we will have 80% power to detect an effect size of approximately 0.8. The standard deviation of the primary GHQ-12 outcome in a generic population of patients with stroke has been shown to be approximately 3.6—this was using the 0 0 1 1 scoring, with total scores ranging from 0 to 12 [60]. This effect size corresponds to an approximate mean difference of 3 points between groups. This sample size is sufficient for these exploratory comparisons; however, in a definitive trial, we would want to have higher power to detect a smaller effect size. This feasibility study will give us a standard deviation specific to the group that we would be interested in recruiting for a definitive trial, so would help to inform such a sample size calculation.

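### The score-based distress response for participants with aphasia rests on the GHQ-12 alone, so those who cannot complete it have a DISCS score but no score trigger or GP prompt

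*Protocol article*

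**What the plan says.** The rule is in the Protocol article under Anticipated risks and benefits. For participants with aphasia and befrienders it reads "If a participant or peer befriender scores within the high emotional distress range of the GHQ-12 (3 or more"; for relatives and other confidants it adds "or the GHQ-28 for significant others (6 or more". Once triggered, "the research assistant or Trial Manager will discuss with them their score and ask them to consider talking to their GP", and details of local support are given to those who want them. The DISCS does not appear in the rule.

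Under Patient-reported outcome measures, both the GHQ-12 and the DISCS are taken at baseline, 4 and 10 months. The reason given for the second scale is: "The DISCS is being measured because some participants may not be able to complete the GHQ-12". No expected rate is given: "This feasibility study will assess how often this is the case". The DISCS takes over as primary outcome if at least 10% of GHQ-12 data are missing because of the severity of aphasia.

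Under Participants with aphasia, a DISCS of 2 or more is "used as a cut-off for identifying depression in those with complex disabilities following brain injury", and at eligibility screening that score leads to referral back to the multidisciplinary team.

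Two provisions do not depend on a score, both under Anticipated risks and benefits: staff and befrienders are trained to respond when someone becomes upset at a visit, and "Information about local support services and voluntary organisations that support well-being post-stroke will be offered to those experiencing low mood".

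**The concern.** The plan has a fallback for its analysis when the GHQ-12 cannot be completed, but none for its safety rule, although both rest on the same questionnaire. A participant who manages only the DISCS could score well above its cut-off at 4 or 10 months, and nothing in the stated rule would make the assessor raise it or suggest the GP.

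The gap is unlikely to fall at random. The article links missing GHQ-12 data to the severity of aphasia, so those without a score trigger are likely to be the people least able to describe their distress unprompted. In the usual care arm there are no befriending visits or befriender supervision, so the assessment visits are the main planned study contact at which distress could be noticed.

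Screening does not fill the gap. For people recruited in hospital, baseline often follows 6 to 8 weeks later, and follow-up runs to 10 months after randomisation. Low distress at entry cannot be assumed to last.

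**Working it through.** **Coverage at the trial assessments, participants with aphasia**

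| Situation at baseline, 4 or 10 months | Score discussed? | GP suggested? | Support information? |
|---|---|---|---|
| GHQ-12 complete, 3 or more | Yes | Yes | Yes, if wanted |
| GHQ-12 not completed, DISCS 2 or more | Not stated | Not stated | Only through the general low-mood provision |
| Visible upset at a visit | Not stated | Not stated | Not stated (break, talk, or stop the session) |

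The second row is a case the article itself anticipates. The only stated action on a DISCS score is at eligibility screening.

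**Number who might be in the second row**

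Inputs from the article:
- 60 recruited, with about 15% loss to follow-up (Sample size).
- "at least 50 will complete the study" (Sample size). Check: 60 × (1 − 0.15) = 51, which agrees.
- Three assessments: baseline, 4 and 10 months (Patient-reported outcome measures).

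Input assumed: GHQ-12 non-completion of 5% to 20% at each visit. The article gives no rate. Its 10% is a threshold for switching the primary outcome, not a forecast.

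Number without a GHQ-12 score = assumed rate × number assessed:
- Baseline: 0.05 × 60 = 3; 0.20 × 60 = 12.
- Each follow-up, 50 retained: 0.05 × 50 = 2.5; 0.20 × 50 = 10.
- All participant-visits, taking 50 at both follow-ups: 60 + 50 + 50 = 160; 0.05 × 160 = 8; 0.20 × 160 = 32.
- For reference, at exactly the 10% switch point: 0.10 × 60 = 6 participants.

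These are counts of people or visits without a GHQ-12 score, not counts of missed distress. The share who would also reach DISCS 2 or more cannot be derived, because entry selects for low distress and the article gives no later DISCS distribution.

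**Partly completed GHQ-12**

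With 0 0 1 1 scoring each item adds 0 or 1, so the total cannot fall as more items are answered. If the answered items already total 3, the existing rule is met whatever the missing answers would have been. The gap is therefore confined to a missing GHQ-12, or an incomplete one with a running total below 3.

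**The case against.** The strongest reply is that this is an article condensing a full protocol. Assessors carry a script with instructions for each measure, the trial has standard operating procedures, and any of these may already act on a raised DISCS. That possibility stands, and the point is limited accordingly. It does not change what the article says: it sets out instruments, cut-offs and actions for three groups rather than leaving the procedure to another document, and that stated rule omits a case the article expects.

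Second, the offer of information to people with low mood is not tied to the GHQ-12, and a raised DISCS is a natural way to recognise low mood. This is a fair reading, and on it the support-information part of the response already reaches these participants. The provision still names no instrument or cut-off and includes no GP suggestion, so the score discussion and the GP prompt remain uncovered.

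Third, the number affected may be small. Entry selects for low distress, people who cannot answer three simple consent questions are excluded, measures are presented in accessible form by skilled assessors, and extra visits are offered to complete them. All of this holds, and it is why no count of missed distress is claimed. The article nevertheless expects some non-completion.

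Fourth, a trigger at 2 could fire at baseline for people admitted with a DISCS of 2 after the multidisciplinary team had considered them. It also treats two people with the same DISCS differently, depending on whether the GHQ-12 was completed. Both are real, so the cut-off should be chosen deliberately. Neither is a reason to have no trigger.

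**Conclusion.** The concern holds. As the article states it, the score-based distress response for participants with aphasia omits those who cannot complete the GHQ-12, although a distress score and a cited cut-off are available for them. They are not without protection; what they lack is a defined score trigger, a discussion of the score and a GP prompt.

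The size is uncertain: 3 to 12 of 60 participants at baseline, about 3 to 10 of 50 at each follow-up, or 8 to 32 of 160 participant-visits. These figures rest wholly on the assumed 5% to 20% non-completion, and the number who would also be distressed is unknown. The conclusion also assumes that Additional file 3 and the assessor script, which were not available, do not already extend the rule to the DISCS. This is a cheap improvement to participant safety; it does not affect the validity of the trial's analysis.

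**What to change.** Add one sentence to Anticipated risks and benefits and to the assessor script, for example:

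> Where the GHQ-12 is missing or incomplete at baseline, 4 or 10 months and the answered items do not already total 3, a DISCS of 2 or more prompts the same response: the score is talked through, the participant is asked to consider seeing their GP, and details of local support are offered.

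The value 2 is the depression cut-off the article already cites. If the clinical leads prefer a different level, for instance because some participants enter with a DISCS of 2, they should fix that level in the text. If Additional file 3 or the script already contains such a rule, it is enough to state it in the section.

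The cost is the sentence itself. The DISCS is already collected at each visit, so no new measure, visit or staff is needed. The downside is a few more conversations for assessors, some of them with people admitted at a DISCS of 2. The same sentence should carry over to any definitive trial.
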